### Analysis population

The primary analysis of the primary outcome will be based on the intention-to-treat (ITT) population. This will include all randomized participants with available data who will be analyzed according to their allocated intervention, regardless of the treatment received.

US Food and Drug Administration regulations recommend that an analysis is performed both as randomized (ITT) and as treatment received (per protocol; PP), aiming to demonstrate noninferiority. Therefore, a secondary analysis will be undertaken on the PP population, which will include all patients who received their allocated treatment and did not have any major protocol deviations. Major protocol deviations will be finalized following a blinded review of the data prior to the primary outcome analysis datalock.

All analyses of the secondary outcomes will be performed for the ITT population.

## Analysis

A separate statistical analysis plan (SAP) with full details of all statistical analyses planned for the data of this study will be made public prior to the study datalock. The SAP was reviewed and received input from the Trial Steering Committee (TSC) and Data Safety and Monitoring Committee (DSMC). Any changes or deviations from the SAP will be described and justified in the protocol, final report, and/or publications, as appropriate. It is anticipated that all statistical analyses will be undertaken using Stata (StataCorp, USA) or other well-validated statistical packages.

Standard descriptive statistics will be used to describe the demographics between the treatment groups reporting means and SD or medians and IQR as appropriate for continuous variables and numbers and percentages for binary and categorical variables. All comparative outcomes will be presented as summary statistics and reported together with 95% CIs.

The PROMIS Upper Extremity Score for Children at three months is the primary outcome of the study and will be compared between treatment groups as the dependent variable in a multivariable linear regression model, adjusting for the stratification factors. An unadjusted *t*-test will also be undertaken. Additional analyses utilizing all the timepoints (from six weeks to one year after randomization) using multilevel modelling will also be undertaken for completeness. Sub-group analysis by fracture type (metaphyseal and Salter-Harris II fractures) will be undertaken using the same methodology by incorporating a treatment by fracture type interaction. Multilevel, mixed-effects, repeated-measures linear regression models will be used to analyze continuous secondary outcomes, if appropriate; otherwise, appropriate non-parametric alternatives will be used. Complications will be reported by type for each treatment group, and, if appropriate, compared between the groups using logistic regression models.

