Pretreatment (clinic)	PROMIS UE baseline, Wong-Baker FACES Pain Scale, EQ-5D-Y
Removal of immobilization (clinic)	Complications
Six weeks	PROMIS UE, Wong-Baker FACES Pain Scale, EQ-5D-Y, VAS cosmesis, complications, school attendance, and economics questionnaire
Three months	PROMIS UE, Wong-Baker FACES Pain Scale, EQ-5D-Y, VAS cosmesis, complications, school attendance, and economics questionnaire
Six months	PROMIS UE, Wong-Baker FACES Pain Scale, EQ-5D-Y, VAS cosmesis, complications, school attendance, and economics questionnaire
One year	PROMIS UE, Wong-Baker FACES Pain Scale, VAS cosmesis, satisfaction score, EQ-5D-Y, complications, school attendance, and economics questionnaire
One year (recruitment centre)	All routinely available radiographs documenting the course of this injury will be collected from the patient record
Two years	PROMIS UE, Wong-Baker FACES Pain Scale, EQ-5D-Y, VAS cosmesis, complications
Three years	PROMIS UE, Wong-Baker FACES Pain Scale, EQ-5D-Y, VAS cosmesis, complications. Any further routinely available radiographs documenting the course of this injury will be collected from the patient record

EQ-5D-Y, youth version of the EuroQol five-dimension questionnaire; PROMIS UE, Patient-Reported Outcomes Measurement Information System, Upper Extremity; VAS, visual analogue scale.

We explored potential outcomes with the parents and children who advise our research. Children believed that early return to normal function was most important to them, and therefore the function at three months was chosen to be the primary outcome. Given the participants’ age, all outcomes will be proxy-reported by the parents, except for pain, which will be child-reported.

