### Randomization

The patient will be randomized after consent and baseline data has been obtained, either in the Emergency Department, or at the first assessment in the fracture clinic. All hospital treatment areas have access to the internet so will access the randomization service in real time, i.e. there will be no delay to patient treatment. Consented participants will be randomized to one of two intervention groups (1:1) using a computer randomization service provided by the Oxford Clinical Trials Research Unit (OCTRU). Randomization allocation will be implemented using a minimization algorithm with stratification factors: centre, type of fracture translation (completely off-ended versus incompletely off-ended), fracture location (metaphyseal or physeal), and age group (four to six years, seven to ten years). The minimization algorithm will be seeded with a number of allocations, and a non-deterministic probabilistic element will be introduced to prevent predictability of the treatment allocation.

Stratification by centre will help to ensure that any clustering effect related to the centre will be equally distributed between the trial groups. Each hospital has a children’s injury unit dealing with these wrist fractures on a daily basis. All of the recruiting hospitals, and all orthopaedic units throughout the NHS, use these techniques as part of their normal fracture management practice, so staff will already be equally familiar with both forms of treatment. This cannot eliminate the clinician-specific effect of an individual at any one centre. However, as the procedures are commonplace across the NHS, many clinicians (15 to 30 at each centre, including consultants and trainees) will be involved in the management of this group of patients. We therefore anticipate that each individual clinician will only treat a handful of those enrolled in the trial, which greatly reduces the risk of a clinician-specific effect on the outcome in any one centre.

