### Sample size

A total of 674 participants providing data on the PROMIS Upper Extremity Score for Children at three months after randomization (337 in each group) will provide 90% power and 2.5% (one-sided) significance to detect whether non-surgical casting for the treatment of displaced wrist fractures is noninferior to surgical reduction, assuming a noninferiority margin of −2.5 points, a SD of 10, and no difference between groups (PASS 16 Power Analysis and Sample Size Software (2018); NCSS, USA). The choice of the noninferiority margin and the baseline SD was based on discussions with patients, their parents, and the literature validating the PROMIS Upper Extremity Score in a range of different diseases. Allowing for 10% loss to follow-up, this yields an overall target of 750 patients (375 per group).

Raw scores of the PROMIS Upper Extremity Score for Children are translated into standardized T-scores with a population mean of 50 and a SD of 10. The minimal clinically important difference (MCID) for the PROMIS Upper Extremity Score among children with mild forms of disability has been demonstrated to be three or four.^28^ In general, the bank of paediatric PROMIS measures have an MCID of three points, in a range of different diseases.^29^ We worked with parents with upper limb injuries to rescore the PROMIS Upper Extremity tools for the vignettes to indicate ‘the minimum difference that is likely to be noticeable’, and ‘the minimum difference that would be necessary to justify undertaking surgery’. Although a score of four points appeared to be the minimal difference noticeable to parents, the clinically important difference required to justify surgery was five points (standardized effect size > 0.5). Parents and children demanded a larger effect size to justify the intervention of surgery. Other studies have similarly highlighted that patients often seek greater effect sizes than the established MCID to warrant surgical interventions.^30^ A noninferiority margin of 2.5 points was decided upon as half the maximum tolerated reduction in acceptability to patients and their parents to justify surgery. If non-surgical casting is shown to be noninferior based on this, then the results are likely to change clinical practice for these fractures.

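### The stated primary model for three-month PROMIS does not name the pre-randomization PROMIS score as a covariate; adding it is a low-cost efficiency gain, not the correction of an error

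*Protocol article*

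**What the plan says.** The Analysis section of the protocol article specifies that the three-month PROMIS score "will be compared between treatment groups as the dependent variable in a multivariable linear regression model, adjusting for the stratification factors". The Randomization section gives the "stratification factors: centre, type of fracture translation (completely off-ended versus incompletely off-ended), fracture location (metaphyseal or physeal), and age group" (four to six or seven to ten years). The baseline value of the outcome is not among them.

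That baseline value is nevertheless collected. Table I (under Aims) lists, for the pretreatment clinic visit, "PROMIS UE baseline, Wong-Baker FACES Pain Scale, EQ-5D-Y". The order of events is also clear: "The patient will be randomized after consent and baseline data has been obtained".

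The other PROMIS analyses do not name baseline either. The supporting t-test is unadjusted. The longitudinal model is described as "Additional analyses utilizing all the timepoints (from six weeks to one year after randomization) using multilevel modelling", so its listed timepoints begin after treatment.

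The Sample size section plans for 674 evaluable children, which "will provide 90% power and 2.5% (one-sided) significance", "assuming a noninferiority margin of −2.5 points, a SD of 10, and no difference between groups". It takes no credit for covariate adjustment.

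**The concern.** A baseline measurement of the outcome, taken before allocation, is a legitimate covariate and often a useful one. Here it is collected, it is not a minimization factor, and the stated adjustment set does not include it.

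Two things are at stake. The first is precision. The noninferiority decision depends on whether the lower 95% confidence limit lies above −2.5 points, a margin of one quarter of the assumed SD. Any avoidable residual variance widens the interval and lowers the chance of a conclusive result. The second is chance imbalance. Minimization does not act on baseline PROMIS directly, so the groups may differ on it by chance. If baseline predicts outcome, part of that difference carries into the unadjusted estimate.

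**Working it through.** **Inputs from the article.** Margin 2.5 points, SD 10, true difference 0, one-sided alpha 2.5%, power 90%, 337 evaluable per group, 10% loss, 1:1 allocation (Sample size and Randomization).

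**Input not in the article.** r, the within-group correlation between baseline and three-month PROMIS given the other covariates. It is treated as an assumption and varied.

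**Step 1: reproduce the plan's figure.** n per group = 2 × (1.960 + 1.2816)² × 10² / 2.5² = 2 × 10.507 × 16 = 336.2, rounded up to 337, so 674 in total. This agrees with the article. Power at 337 per group is 90.1% by the normal approximation and 89.98% by the noncentral t. For loss to follow-up, 674 / 0.90 = 748.9, rounded up to 749 and then to 750 for equal groups. This also agrees.

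**Step 2: power and precision with baseline in the model.** The residual SD becomes 10 × √(1 − r²).

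- SE = 10 × √(1 − r²) × √(2/337)
- power = Φ(2.5/SE − 1.96)
- 95% CI half-width = 1.96 × SE
- evaluable N for 90% power = the step 1 formula with the smaller SD

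| assumed r | residual variance vs no adjustment | power at 674 | CI half-width (points) | N for 90% power |
|---|---|---|---|---|
| 0 | 1.00 | 90.1% | 1.51 | 674 |
| 0.1 | 0.99 | 90.3% | 1.50 | 666 |
| 0.3 | 0.91 | 92.5% | 1.44 | 612 |
| 0.5 | 0.75 | 96.3% | 1.31 | 506 |

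Worked line for r = 0.3: SE = 10 × 0.9539 × 0.07704 = 0.735; 2.5 / 0.735 − 1.96 = 1.44; Φ(1.44) = 92.5%.

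**Step 3: effect of a chance imbalance.** Assume that baseline and three-month scores both have SD 10, so that the regression slope equals r. The standard error of the baseline difference is then 10 × √(2/337) = 0.770 points. An imbalance of that size shifts the estimate by r × 0.770 if baseline is not in the model:

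- r near 0: no shift
- r = 0.3: 0.23 points, or 9% of the margin (0.231 / 2.5)
- r = 0.5: 0.39 points, or 15% of the margin (0.385 / 2.5)

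**The case against.** The strongest reply is that the sentence need not be a closed list. The Introduction calls the article an abridged protocol, and the Analysis section leaves full detail to a separate SAP that is not shown here. That SAP may already contain baseline PROMIS. This stands as a caution: the article never says that it adjusts for these factors and nothing else. It does not remove the point, because the article does state an adjustment set for the primary model and baseline is not in it.

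The second reply is that r may be low. Baseline is recorded in the Emergency Department or at the first fracture clinic assessment, within seven days of injury. The article does not say whether the answers describe function before the injury or with the broken wrist. Scores with an acutely broken wrist may predict recovery poorly. Recalled pre-injury function may vary little, since children with developmental delay or abnormality are among those excluded. The relevant r is also what remains after age group and fracture type are in the model. All of this stands, and it is why no single figure for the gain can be given.

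Three stronger readings are tempting, and the article does not support them.

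- A reader might infer that the primary analysis is biased or underpowered. Randomization makes the stated comparison valid, its confidence interval already allows for chance imbalance on average, and 674 reproduces with no help from baseline.
- A reader might infer that a baseline imbalance passes into the estimate in full. It does so only in proportion to the baseline–outcome slope, as step 3 shows.
- A reader might infer that the secondary models for pain and EQ-5D-Y also leave out their baselines. The article names no covariates for those models, and that detail properly belongs to the SAP.

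**Conclusion.** The point holds as an efficiency and chance-imbalance improvement to the primary model. It is not an error in the plan. The article states an adjustment set that omits a prognostic candidate collected before randomization on the same scale as the outcome. Power at 674 would rise by about 0.3 percentage points at r = 0.1, 2.5 at r = 0.3 and 6.2 at r = 0.5 (96.3 − 90.1), with no gain if r is near 0. These figures rest on an SD of 10, a true difference of zero, full evaluable numbers and an r that the article does not supply. The figures for the shift in the estimate also assume equal SDs at baseline and three months. One extra continuous covariate among 674 children costs a single degree of freedom, so there is little to lose if r proves small.

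**What to change.** Before datalock, amend the primary model to a linear regression of three-month PROMIS on treatment, the stratification factors and continuous baseline PROMIS Upper Extremity score. State how missing baseline values are handled, either by simple mean imputation across both groups or by a missing indicator, so that no randomized child with a three-month score is lost from the analysis. Leave 674 and 750 unchanged; they are then conservative.

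The cost is a line of text and no new data. The article says that the SAP has already been reviewed by the steering and data monitoring committees, so the change may need a documented SAP amendment. If the SAP already includes baseline PROMIS, only the protocol wording needs to be aligned with it.

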### Health economic evaluation

An economic evaluation of surgery compared with cast immobilization will be conducted from the UK NHS and PSS using the CRAFFT trial data.^31^ A Health Economics Analysis Plan, providing full details of the prospective economic analysis is appended to this document. Health-related quality of life will be estimated using the EuroQol EQ-5D-Y.^18,24^ EQ-5D-Y responses will be valued using the most appropriate valuation set available for the trial population at the time of analysis. If necessary, the adult EQ-5D-3L will be applied, in which case we will undertake sensitivity analysis to make sure that trial findings are not sensitive to the valuation set chosen.^32^ Using the trapezoidal rule, the area under the curve of health status scores will be calculated, providing patient-level quality-adjusted life year (QALY) estimates. Participants’ health service contacts, made in connection with the child’s injury, will be recorded at six weeks, and three, six, and 12 months. Index interventions and subsequent healthcare resource use will be costed using the most recently available published national reference costs, reflated to a common year.^33,34^ Parents’/carers’ out-of-pocket expenses and time lost from work (paid/unpaid) because of their child’s condition, and time off from school, will also be recorded. Resource use questionnaires will be completed by each child’s parent/carer as a proxy response. Mechanisms of missingness of data will be explored, and multiple imputation methods will be applied to impute missing data. Imputation sets will be used in bivariate analysis of costs and QALYs to generate within-trial (12-month) incremental cost per QALY estimates and CIs.^35-38^ Findings will be analyzed and visualized in the cost-effectiveness plane, as cost-effectiveness acceptability curves, net monetary benefit, and value of information analysis. If incremental costs and benefits are non-convergent within the trial follow-up, then extrapolated modelling will be considered, drawing upon epidemiological sources. Sensitivity analyses will be conducted to consider the broader issue of the generalizability of the study results and consider the impact of a broader societal perspective.

### Qualitative study of recruitment and experience of treatment interventions

A qualitative study will be undertaken to identify barriers and facilitators to recruitment. The aim is to increase understanding of the impact of injury and inform practical strategies to improve the process of recruitment in the main trial, for example developments in the presentation of study information. To achieve this, the study will explore: 1) parents’ and children’s experience of injury, treatment, and its impact on their daily life; 2) parents’ and children’s experience of being asked to participate in a randomized controlled surgical trial; and 3) staff experience of being involved in a paediatric surgical trial. To achieve this, qualitative interviews will be incorporated throughout the study. A full description of the qualitative work is available in the complete protocol online on the NIHR website.

### Quality control

This study will be coordinated by the UK Clinical Research Collaboration-registered OCTRU at the University of Oxford. We will institute a rigorous programme of quality control. The trial management group will be responsible for ensuring adherence to the trial protocols at the trial sites. Quality assurance checks will be undertaken by the central trial team to ensure integrity of randomization, study entry procedures, and data collection. The Clinical Trials Unit (CTU) has a quality assurance manager who will monitor this trial by conducting inspections (at least once in the lifetime of the study and more if deemed necessary) of the trial master File. Furthermore, the processes of consent taking, randomization, registration, provision of information, and provision of treatment will be monitored by the central trial team. Written reports will be produced for the TSC, informing them if any corrective action is required.

Additionally, the study may be monitored or audited by sponsor or host sites in accordance with the current approved protocol, GCP, relevant regulations, and SOPs.

### Patient and public involvement

Patients and children were involved from the inception of the trial, including in the development of the funding application. The study was discussed in detail with members of the NIHR Young Person’s Advisory Group,^41^ who chose the logo for the study from an online design competition. An ongoing commitment has been made to continue to work with this group in the production of patient-facing materials and the study dissemination plan.

To ensure ongoing patient and public involvement, a patient/carer representative will be actively involved in general trial management. In addition, a further independent patient/carer representative will become a member of the steering committee.

### Ethics and dissemination

The National Research Ethics Committee approved this study on 16th April 2020 with reference number 20/WM/0054. The full study report for the NIHR Health Technology Assessment will be prepared by the trial management team upon completion of the trial. A manuscript for a high-impact, peer-reviewed journal will be prepared simultaneously, which will allow for the results to be disseminated across the orthopaedic and emergency medicine communities, the wider medical community, the National Institute for Health and Care Excellence, and policy makers. Authorship will be determined in accordance with the International Committee of Medical Journal Editors guidelines, and other contributors will be acknowledged. The results of this trial will substantially inform clinical practice on the clinical and cost-effectiveness of the treatment of this injury. The results of this project will be disseminated to patients via patient-specific newsletters and through local mechanisms at all participating centres.

**Take home message**

- The Children’s Radius Acute Fracture Fixation Trial (CRAFFT) is a multicentre randomized controlled study evaluating surgical versus non-surgical management of displaced distal radius fractures in children.

- The findings may have far-reaching implications for the treatment of distal radius fractures in children.

## Data Availability

The data that support the findings for this study are available to other researchers from the corresponding author upon reasonable request.
